### Data management and quality control

2.6

Patients will be required to complete the EXACT-Pro questionnaire delivered via a WeChat mini program at 9:30 a.m. daily. Research assistants will check the questionnaire completion status at 7:00 p.m. and remind patients via telephone to complete it promptly. Research assistants will also call patients weekly to inquire about their respiratory symptoms over the past week and provide verbal reminders to take their medication regularly.

To minimize measurement errors, each participant will be assessed by the same evaluator during every visit. Study data will be stored on a password-protected platform and backed up to a secure external hard drive; data access will be restricted only to authorized researchers and staff. Automatic plausibility controls will be implemented during data entry to detect any inconsistencies or inaccuracies.

### Statistical analysis

2.7

Data analysis will follow the modified intention-to-treat principle to ensure complete randomization, minimize selection bias, and reflect real clinical practice. Missing data will be addressed using multiple imputation to reduce potential bias resulting from missing information, ensuring the robustness and accuracy of the analysis. All statistical tests will be performed according to a preestablished statistical analysis plan. SPSS (version 21.0) will be used for all data analyses, and two-tailed *p* < 0.05 will be considered to indicate statistical significance.

Continuous variables will be expressed as means ± standard deviations or median (Interquartile) where appropriate, and categorical variables as frequencies and percentages. Normality testing for continuous variables will be performed using the Shapiro–Wilk or Kolmogorov–Smirnov test, and homogeneity of variance will be assessed using the Levene test. For continuous variables that are normally distributed with equal variance, intergroup comparisons will be conducted using the independent-samples *t*-test. For continuous variables that do not meet the normality or homogeneity assumptions, the Mann–Whitney *U*-test will be employed. For discrete variables (such as the AE number and severity over 12 weeks), intergroup comparisons will be performed using the chi-square, Fisher exact, or Cochran–Mantel–Haensel χ^2^ test.

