### Study design

2.1

This will be a single-center, prospective, and parallel randomized controlled trial. Participants will be randomly assigned to a VIT or TIE group for corresponding interventions and follow-up. The study period will begin 1 week before discharge and include a 12-week follow-up after discharge. Outcomes will be measured at baseline (V0), after instruction (V1), before discharge (V2), and at week 12 after discharge (V3).

This trial is registered at ClinicalTrials.gov (registration number: ChiCRT2500097816) on 26/02/2025. The study protocol is reported according to the Standard Protocol Items: Recommendations for Intervention Trials 2013 (19) guidelines, and the intervention procedures are described according to the Consolidated Standards of Reporting Trials (CONSORT) 2025 Checklists. Figure 1 illustrates the CONSORT flow diagram for this study, and Table 1 summarizes the study schedule and assessments.

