**Pulmonary function**						
FVC & FVC%				✓		✓
FEV1 & FEV1%				✓		✓
FEV1/FVC				✓		✓

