### Randomization, allocation concealment, and blinding

2.3

All patients will be randomly allocated at a 1:1 ratio to either the VIT or TIE group by using a random number table generated by an independent statistical analyst with SPSS. In accordance with the 2025 WHO age classification, participants will be stratified into two age groups (40–65 years and 66–85 years) before randomization to ensure balanced distribution across intervention arms. The assignment details will then be sealed in opaque envelopes. After each participant provides written informed consent and completes their baseline assessments, the study coordinator will open the envelope to reveal the participant's group allocation.

Because of the nature of the intervention, neither the participants nor the instructors will be blinded; nevertheless, the outcome assessors and statistical analysts will remain blinded to group assignments.

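### Continuous secondary outcomes go to an unadjusted t-test or Mann–Whitney test picked by pre-tests, so the quantity tested is not fixed and the V0 values and age stratum go unused

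*Protocol article*

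**What the plan says.** All places are in the protocol article.

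- **Choice of test (2.7 Statistical analysis).** "Normality testing for continuous variables will be performed using the" Shapiro–Wilk or Kolmogorov–Smirnov test, and "homogeneity of variance will be assessed using the Levene test". Then: "For continuous variables that are normally distributed with equal variance, intergroup comparisons will be conducted using the independent-samples" t-test. The other branch begins "For continuous variables that do not meet the normality or homogeneity assumptions" and leads to the Mann–Whitney U-test. Neither branch names a covariate, a baseline value or a stratum.
- **Discrete variables (2.7).** "For discrete variables (such as the AE number and severity over 12 weeks), intergroup comparisons will be performed using the chi-square, Fisher exact" or Cochran–Mantel–Haenszel test. This last is the only stratified method listed, and its stratum is not named.
- **Randomization (2.3).** "participants will be stratified into two age groups (40–65 years and 66–85 years) before randomization". The envelope is opened only after the baseline assessments are complete, so V0 values precede allocation.
- **Visits (2.1 and Table 1).** "Outcomes will be measured at baseline (V0), after instruction (V1), before discharge (V2), and at week 12 after discharge (V3". Table 1 has V0 entries for PIFr, EIT, EIV, the IIFS score, the inhalation checklist and TAI. The rows under "Pulmonary function", and those for MIP/MEP, grip strength, knee extension, 6MWT, mMRC and CAT, have entries at V2 and V3 only.

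**The concern.** Three features of the stated rule call for change.

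1. **The question depends on the data.** A t-test compares means. A Mann–Whitney test asks whether values in one arm tend to be larger. Which of the two is reported for an outcome depends on pre-tests of modest power and with their own false alarms.
2. **Unequal variance is sent to the wrong remedy.** If only the spread differs, a Welch test or robust standard errors would keep the comparison of means. Mann–Whitney replaces it with another comparison and yields no mean difference. Unequal spread is plausible here: VIT trains patients towards a target flow, which could narrow PIFr in one arm.
3. **Information already collected is not used.** The technique measures and TAI have true pre-allocation values, and age was judged important enough to stratify on. Neither enters the comparison as written.

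At stake is the precision and interpretability of the secondary outcomes in a trial of 80 patients.

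**Working it through.** **Number evaluable.** Section 2.8 gives event rates of 48.9% and 15%, σ = 0.614, Δ = 0.339, Z values of 1.96 and 0.84, and 20% dropout.

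- σ = √(0.489×0.511 + 0.15×0.85) = √0.3774 = 0.614.
- n = (0.614 × 2.80 / 0.339)² = 25.7; 25.7/0.8 = 32.1. This reproduces the stated 32.
- 40 recruited × 0.8 = 32 evaluable per arm if the assumed dropout occurs.

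That calculation concerns the primary outcome. Here it only supplies the 32.

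**Precision lost by leaving out V0.** With correlation r between V0 and V3, ANCOVA multiplies the variance by (1 − r²). The effective number per arm is 32/(1 − r²). The effect detectable with 80% power at two-sided 0.05 is (1.960 + 0.842) × √(2/32) × √(1 − r²) = 0.70 × √(1 − r²) SD. The documents give no r, so the values are assumed.

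| r | 1 − r² | Effective n per arm | Detectable effect (SD) |
|---|---|---|---|
| unadjusted | 1.00 | 32 | 0.70 |
| 0.3 | 0.91 | 35.2 | 0.67 |
| 0.5 | 0.75 | 42.7 | 0.61 |
| 0.6 | 0.64 | 50.0 | 0.56 |
| 0.7 | 0.51 | 62.7 | 0.50 |

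**Leaving out the age stratum.** Suppose the strata are of equal size, the arms are balanced within each, and the strata differ by f residual SDs. The t-test then overstates the variance by the factor 1 + f²/4. Its type I error is about 2[1 − Φ(1.96√(1 + f²/4))]:

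| f | Formula | Simulated (5,000 trials, 32 per arm) |
|---|---|---|
| 0.3 | 4.7% | 4.7% |
| 0.5 | 4.3% | 4.3% |
| 0.8 | 3.5% | 3.3% |
| 1.0 | 2.8% | 3.1% |

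**The pre-test gate.** The rule was simulated with Shapiro–Wilk in each arm, Levene, 5% cut-offs (assumed), 32 per arm and 5,000 trials per setting. The Monte Carlo error near 5% is about √(0.05×0.95/5000) = 0.3 percentage points.

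| Data in the two arms | Sent to Mann–Whitney | Gate rejects | Welch rejects |
|---|---|---|---|
| Same normal | 13.5% | 5.1% | 5.3% |
| Same lognormal | 94.9% | 4.5% | 4.3% |
| Normal, SD 1 vs 2 | 93.1% | 5.4% | 4.9% |
| Lognormal, equal means, σ 0.3 vs 0.8 | 99.5% | 42% | 7.7% |

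In the first row, about one comparison in seven changes test by chance alone. In the last row both means are 1 (exp(−0.045 + 0.3²/2) and exp(−0.32 + 0.8²/2)), but the medians are exp(−0.045) = 0.96 and exp(−0.32) = 0.73. Mann–Whitney detects that rank shift, so the row shows a change of question.

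**Which outcomes have a usable baseline.** Setting Table 1 beside section 2.3, only the technique measures and TAI are measured before allocation. V2 comes after V1, the visit after instruction, so it follows both randomization and instruction.

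**The case against.** **The analysis is valid as it stands.** This objection stands. An unadjusted comparison of randomized arms is unbiased, and its standard error already allows for chance baseline imbalance. A reader might infer that imbalance invalidates the week-12 results or inflates false positives. The documents do not support that: the gate rejected in 4.5% to 5.4% of simulated trials when the arms shared a distribution or were normal with unequal spread, and ignoring the stratum lowers the error rate.

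**The 42% figure is contrived.** It needs strongly different skew with the means forced equal, and nothing in the documents points to such data. It should not be read as the false-positive rate of the plan.

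**The separate SAP may adjust.** Section 2.7 refers to a pre-established plan that is not shown, and the article does not say whether V3 or a change is compared. Silence on covariates alone would be no finding. But the article does positively state the gate and its two unadjusted tests, and an SAP with one adjusted model would contradict that rule. If a change from V0 is meant, its variance factor is 2(1 − r): 1.4, 1.0, 0.8 and 0.6 at r = 0.3, 0.5, 0.6 and 0.7. ANCOVA is more precise at each value.

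**The gain may be small.** VIT is meant to change technique, so a high correlation between V0 and V3 cannot be presumed. At r = 0.3 the gain is about 3 patients per arm. It does not extend to lung function, strength, 6MWT or CAT, which have no V0 value.

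**V2 is never called a baseline.** Correct. A reader might infer from Table 1 that V2 will serve as one for the outcomes first measured there. No section says so, and a comparison at V3 is unaffected by when V2 falls. The point is only a caution.

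**Some measures may fall outside the rule.** mMRC is ordinal, the checklist may not be continuous, and TAI is also grouped into three levels. Only the TAI score is counted here.

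**Conclusion.** The point holds as one of efficiency and definition for secondary outcomes; it does not show bias. The stated rule lets pre-tests decide what is compared, answers unequal variance with a test that does not compare means, and uses neither V0 nor the age stratum.

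The precision forgone is equivalent to moving from 32 to about 35–63 per arm. This rests on assumed correlations of 0.3 to 0.7 and on 20% dropout, and it applies only to PIFr, EIT, EIV, IIFS score and TAI score. The conservatism from ignoring age is slight, from nearly none to a type I error of about 3% for an assumed age effect of 0.3 to 1.0 SD. It arises only if stratification does balance the arms within age groups.

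**What to change.** - Remove the normality and Levene gate from section 2.7 and name one analysis per outcome.
- **Continuous outcomes with a V0 value (PIFr, EIT, EIV, IIFS score, TAI score):** ANCOVA of V3, and of V1 where measured, on group, V0 value and age stratum, with robust standard errors. Report the adjusted mean difference with its 95% confidence interval.
- **Continuous outcomes first measured at V2 (lung function, MIP/MEP, grip strength, knee extension, 6MWT, CAT):** compare V3 between groups adjusted for age stratum, with robust standard errors. State that V2 is a post-instruction measurement and will be neither a covariate nor the reference for a change score.
- **mMRC and other ordinal or categorical measures:** name a method suited to the scale.
- Align the SAP with this text.

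The cost is wording only: no further patients, visits or measurements. Taking CAT and mMRC at V0 before the envelope is opened would give them a true baseline, but that is an optional extra collection.

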## Background

1

Chronic obstructive pulmonary disease (COPD) is a progressive disorder characterized by persistent inflammation of the airways, alveoli, and microvasculature, primarily manifested by irreversible airflow limitation (1). Acute exacerbations (AEs) are major negative events occurring in the course of COPD. Clinical observations have demonstrated that patients experiencing frequent AEs of COPD (AECOPD) have a significantly faster decline in lung function indicators, such as forced expiratory volume in 1 s (FEV1) and peak expiratory flow (PEF), compared to those with a stable disease (2). After the occurrence of an AE requiring hospitalization, the risk of mortality in the short term increases significantly (3, 4). Even after remission, patients with AECOPD have a high recurrence risk. In patients with AECOPD, the rate of AE recurrence within 90 postdischarge days can be as high as 48.9% (5). The more frequent the recurrences, the higher the mortality rate (4). Therefore, reducing AE recurrence is essential for improving the quality of life and reducing mortality, healthcare visit frequency, and medical costs among affected patients with COPD (6, 7). According to the 2024 report of the Global Initiative for Chronic Obstructive Lung Disease (GOLD), inhaler therapy is the preferred treatment for stable COPD patients, and correct use of inhaled medications can reduce the mortality risk in patients with a history of frequent AEs, severe AEs, or both significantly (8, 9).

During inhalation therapy, the drug delivery and deposition process involves the medication traveling through the oral cavity and pharynx, followed by its entry into the trachea, bronchi, and small airways, and ultimately its arrival and deposition into the alveoli and small airways. Here, the patient's mastery of the correct inhalation technique mainly influences the effectiveness of drug delivery and deposition. In particular, this effectiveness is closely related to not only the appropriate maintenance of inspiratory flow rate but also the proper execution of inhalation techniques.

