#### Primary outcome

2.5.1

The primary outcome of this study will be AE frequency within 12 weeks after discharge, which will be monitored weekly via telephone.

The GOLD 2024 guidelines define AECOPD as a sudden worsening of respiratory symptoms, with dyspnea as the primary symptom. Secondary symptoms may include increased sputum volume and thickness, aggravated coughing, and wheezing. During this study's weekly follow-ups, an AE will be recorded if the patient experiences a significant worsening of dyspnea (primary symptom) lasting for ≥2 days or if two or more secondary symptoms worsen beyond normal daily variation over ≥2 days. The duration of each exacerbation will be carefully documented to prevent record duplication during subsequent follow-ups. A structured interview and record form will be developed to capture data on the number of AECOPD exacerbations over 12 weeks after discharge. See Appendix 1 for additional details.

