### Sample size calculation

2.8

Our literature review indicated that the AE rate within 3 months after hospitalization for AECOPD is approximately 48.9% (5). Our preliminary data (unpublished) indicate that after VIT, the treatment failure rate at 90 days is approximately 15%. Therefore, the expected effect size between the two groups is about 33.9%. We set the significance level α = 0.05 and the statistical power at 80% (i.e., β = 0.20), with a dropout rate assumed to be 20%. The calculated values for *Z*_α_/2 and *Z*β are 1.96 and 0.84, respectively, with standard deviation σ = 0.614, effect size Δ = 0.339. Based on these parameters and sample size calculations, each group must include ≥32 patients. To ensure data accuracy and account for potential dropouts, we plan to recruit 40 patients per study group, totaling 80 participants.

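### The number of AEs is to be compared by chi-square-type tests with no named stratum or covariate; a prespecified count model with age stratum and previous AE count would be more precise

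*Protocol article*

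**What the plan says.** Section 2.5.1 makes the primary outcome a count: "The primary outcome of this study will be AE frequency within 12 weeks after discharge, which will be monitored weekly via telephone". Section 2.7 assigns that count to contingency-table methods: "For discrete variables (such as the AE number and severity over 12 weeks), intergroup comparisons will be performed using the chi-square", and the list goes on to the Fisher exact test and ends with the CMH test. The section does not say which of the three applies to the primary outcome, how the count is to be tabulated, or what would define the CMH strata. No regression model is named.

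In section 2.3, "participants will be stratified into two age groups", 40–65 and 66–85 years. Age is the only stratification factor. In Table 1, AE frequency and severity appear only in the follow-up column. Table 2 has no criterion on earlier exacerbations. The Background does mention patients with such a history, in a sentence about inhaled treatment and mortality: "in patients with a history of frequent AEs, severe AEs, or both".

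Section 2.7 also refers to a preestablished statistical analysis plan, which is not shown.

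**The concern.** Patients differ in how often they exacerbate. For an outcome that counts exacerbations, a patient's own past count is the natural baseline measure. As stated, the analysis leaves that variation in the error term. If one arm happens to receive more frequent exacerbators, nothing in section 2.7 allows for it.

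There is a second loss. If the count is reduced to a two-by-two table, one AE and three AEs are treated alike. With at least 32 patients per group needed and 40 recruited, the trial has little precision to spare unless the true effect is as large as the planning value.

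**Working it through.** **Inputs from the article (sections 2.7 and 2.8).** Two-sided 5% level; control: "the AE rate within 3 months after hospitalization for AECOPD is approximately 48.9" percent; VIT 15%; σ = 0.614; Δ = 0.339; dropout 20%; at least 32 per group, 40 recruited.

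**The plan's own figure.** σ equals √(0.489 × 0.511 + 0.15 × 0.85) = 0.614, so it already carries both arms' variance. Then n = (1.96 + 0.84)² × 0.614² / 0.339² = 25.7 per group; 25.7/0.8 = 32.1 and 32/0.8 = 40. The stated figures reproduce, apparently with dropout applied twice. No covariate enters. With 32 evaluable per group, z = 0.339 × √32 / 0.614 − 1.96 = 1.16, a power of 0.88 at the planning effect.

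**Not in the article, so assumed.** The link between past and future AEs, the share of frequent exacerbators, and the overdispersion.

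**1. Precision, same formula.** Multiply the variance by (1 − R²), where R² is the share of outcome variance explained by history:

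| R² | n per group | Power at 32 |
|---|---|---|
| 0 | 25.7 | 0.88 |
| 0.05 | 24.4 | 0.89 |
| 0.10 | 23.1 | 0.91 |
| 0.20 | 20.6 | 0.94 |
| 0.30 | 18.0 | 0.96 |

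**2. Chance imbalance, 40 per arm.** If 32 or 40 of the 80 are frequent exacerbators, the exact hypergeometric probability of a gap of 15 points or more between arms (6 or more patients of 40) is 0.254 or 0.263. The effect of a gap, at a 50% share: if frequent exacerbators have twice the rate, a 10-point gap gives (1 + 0.55)/(1 + 0.45) = 1.07; at three times the rate, (1 + 2 × 0.55)/(1 + 2 × 0.45) = 1.11. A 20-point gap gives 1.6/1.4 = 1.14 and 2.2/1.8 = 1.22.

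**3. Test versus count model.** Simulation with 32 per arm, dispersion 0.5, half the patients frequent exacerbators, control probability of any AE set to 48.9%, 1,500 trials per row. The count model is quasi-Poisson.

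| True rate ratio | Rate ratio for history | Chi-square, any AE | Count model | Count model + history |
|---|---|---|---|---|
| 0.5 | 1.5 | 0.355 | 0.444 | 0.463 |
| 0.5 | 2 | 0.345 | 0.437 | 0.460 |
| 0.5 | 3 | 0.277 | 0.381 | 0.459 |
| 0.21 (planning effect) | 1.5 | 0.871 | 0.917 | 0.924 |
| 0.20 (planning effect) | 2 | 0.861 | 0.933 | 0.942 |
| 0.19 (planning effect) | 3 | 0.865 | 0.921 | 0.949 |
| 1.0 (null) | 1.5 | 0.070 | 0.061 | 0.061 |
| 1.0 (null) | 2 | 0.061 | 0.055 | 0.058 |

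At a rate ratio of 0.5 the count model gains 9 to 10 points over chi-square, and history adds 2 to 8 more. Over a wider set of assumptions at rate ratios 0.4 to 0.5, the first gain was about 3 to 10 points. The null rows show that it is not bought with a higher type I error.

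**4. How far the history gain depends on the link.** Quasi-Poisson with and without log(previous count + 1), 32 per arm, control mean −ln(1 − 0.489) = 0.671, dispersion 0.4, 0.7 and 1.0, 1,000 trials each:

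- Past and future counts share the same patient rate, rate ratio 0.5: power 0.345→0.367, 0.343→0.386, 0.325→0.392.
- The same at rate ratio 0.4: 0.541→0.570, 0.481→0.559, 0.446→0.562.
- Over repeats of these two settings, the standard error fell by about 2 to 13%.
- Only half the patients keep the same rate, rate ratio 0.5: 0.400→0.405, 0.345→0.366, 0.316→0.322. The standard-error ratio is 0.99 to 1.00.

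Type I error with adjustment was 0.04 to 0.07 over repeats, no worse than without it (0.05 to 0.08 in the repeat that recorded both).

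**The case against.** The strongest reply is that covariates and the list of baseline characteristics belong in the statistical analysis plan or the full protocol, and the article cites such a plan. This stands in part: the unseen plan may name strata or covariates. But section 2.7 does not leave the comparison of AE number open. It names the tests, and a better method can be judged against them.

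Three stronger readings are tempting, and the article does not support them.

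- *The comparison is wholly unadjusted.* CMH is a stratified test and age is a stratification factor, so an age-stratified analysis may be intended. What can be said is that no stratum is named. Age is also no direct measure of exacerbation tendency.
- *Exacerbation history will not be collected.* Table 1 has no row for any patient characteristic, not even age, which must be recorded to form the strata. Its silence proves little, and the appendix with the AE interview form is not shown.
- *The Background calls past AEs a predictor of later AEs.* It links frequent AEs to lung-function decline and mortality. It does not say that earlier AE count predicts AE count after discharge; that premise is an assumption here.

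It is also right that randomization keeps the test valid: its error rate already allows for chance imbalance, so this is not bias. Finally, adjustment does not rescue a small effect. At a rate ratio of 0.5, power stays below one half in every setting above.

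**Conclusion.** The point holds as one of efficiency. The stated tests for AE number name no stratum and no covariate and, if applied to any AE versus none, discard information in the count. The steadier gain comes from analysing the count as a count: about 3 to 10 power points at rate ratios 0.4 to 0.5 with 32 per arm. History cuts the standard error by a further 0 to 13%. The upper end needs past and future counts to share one patient rate; the lower end applies when the link is weak.

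At the planning effect the difference is smaller: about 0.86–0.87 for chi-square, 0.92–0.93 for the count model and 0.92–0.95 with history. The change therefore matters mostly if the true effect is below the planning value, whose 15% comes from unpublished preliminary data.

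The figures take chi-square on any AE as the reading of section 2.7. This fits the proportions used for sample size, but the section does not say so, and a table of several count categories would perform differently.

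**What to change.** In section 2.7, replace the chi-square-type test for AE number with one prespecified overdispersed count model (negative binomial or quasi-Poisson), reporting the rate ratio, with treatment arm, age stratum and log(previous-12-month AE count + 1) as terms. In the V0 column of Table 1, add the number of AEs and of AECOPD admissions in the 12 months before the index admission, recorded before allocation. The timing matters because participants are not blinded and recall after allocation could be coloured by it.

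The cost is one chart item or question and one more model term, with no extra patients. Past mild AEs will be recalled imperfectly. Recorded before allocation, such error shrinks the gain but does not bias the comparison. If the unseen analysis plan already specifies such a model, it is enough to bring section 2.7 and Table 1 into line with it.
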